# **Executive summary**

## **context**

More than 47 million children suffered from acute malnutrition around the world before the COVID 19 pandemic. Disruption of economic systems, decline in access to health and nutrition services resulted in an increase of 20 % (or approximately 10.4 million new children) of the number of children who would suffer from acute malnutrition in 2021 mainly in low and middle income countries (Asia and Sub-Saharan Africa including the DRC). It is in this context that UNICEF, UNSCN, PAM and WHO insist on the immediate implementation of 5 urgent actions, including the early detection and treatment of wasting (acute malnutrition) in children. The treatment of uncomplicated SAM is community-based using systematic medical and nutritional treatment (distribution of Ready-to-Use Therapeutic Foods, RUTF) according to the strategy of community-based care of acute malnutrition (PCMA). Previous evaluations have shown that CMAM remains effective in the management of SAM despite low body weight gain, possibly due to inadequate practices (sale, sharing of RUTF, misuse of RUTF, lack of time to deal with patients. children ...), compared to treatment at the hospital. Studies (COMPAS, OPTIMA and MANGO) have tested the effectiveness of a reduced dose of RUTF under certain conditions and among different populations. The MANGO study confirmed the efficacy of a reduced dose in uncomplicated SAMs living in eastern Burkin Faso, under artificially ideal conditions. This is how the EfRAMAS project is proposed in order to assess the effectiveness of a reduced dose of RUTF without additional staff to collect data including a certain food insecurity in the DRC.

## **Goals**

To assess the effectiveness of a reduced dose of RUTF on the speed of weight gain in children aged 6 to 59 months suffering from severe acute malnutrition, without medical complications in a context of food insecurity and without additional personnel to collect the data. The additional objectives are to evaluate the effect of the reduced dose of RUTF on the melting of edema, performance indicators (cure rate, abandonment rate, death rate, internal reference rate) and duration processing. In addition, the psychomotor development of children during the management of SAM, the degree of acceptance of the reduced dose by local communities and the food security situation of study participants will be assessed.

## **Intervention**

The children admitted to this study will be divided into two groups: control and intervention. For the first two weeks, all children in both groups will receive the same standard dose of RUTF. From the third week, the dose of RUTF will be reduced for the intervention group according to their weight.

## **Study design**

The EfRAMAS project is a randomized, controlled, non-inferiority study without additional staff to collect data and in a food insecure situation in children with SAM without medical complications. Children admitted to the study will be individually randomized into two groups, one receiving the standard dose (control) and the other the reduced dose (intervention). They will be closely monitored with weekly anthropometric and clinical measurements taken by the usual staff of the health centers and with the support of ACF supervisors, in order to assess the good progress of recovery.

## **Methodology**

Anthropometric measurements including weight, height, MUAC and nutritional edema will be taken once a week on each child, from admission to discharge, using tools (scales, measuring rod, PB tape, ...) Existing in health centers. The age and sex of the children will also be entered upon admission in order to help calculate the anthropometric indicators.

Psychomotor Development will be assessed by analyzing the skills and abilities acquired in the four main areas on admission, on discharge and then in the sixth month.

Food security will be assessed on admission according to the household food insecurity access scale (HFIAS) method proposed by the Food and Nutrition Technical Assistance Project (FANTA). Food and Nutrition).

Under study, a qualitative survey using focus groups, in-depth interviews and field observations will make it possible to assess the degree of acceptance of the reduced dose of RUTF by local communities and by nursing staff.

An economic evaluation of the cost of treatment will be made during the study by comparing the reduced dose approach to the standard dose approach.

## **Participants**

All SAM children without medical complications from 6-59 months according to the national protocol (PT index  $< -3$  Z score and / or PB  $< 115$ mm and / or bilateral edema (+, ++)) as well as a positive appetite test ) are eligible for the study. The information about the study will be explained to the parents or legal guardians in the local language, the latter will have the choice to refuse or to involve their children in the study. If the parents or legal guardians agree to have their children participate in the study, they will sign a free and informed consent. Parents or legal guardians refusing their children to participate in the study will have access to the uncomplicated SAM management program in force at the same health center. SAM children with complications, with negative appetite for RUTF, will be excluded from the study, or those whose parents or legal guardians have refused to participate. A unique identifier (ID) will be assigned to each enrolled child. The list of names of the children participating in the study with

their identifier will be kept under lock and key in each health center, in order to guarantee confidentiality throughout the study. MAS children will be recruited at the UNTA level, whether they come directly from the community or whether they are referred from preschool consultations (CPS). Community intermediaries will ensure awareness-raising on acute malnutrition in order to facilitate recruitment on time. The list of names of the children participating in the study with their identifier will be kept under lock and key in each health center, in order to guarantee confidentiality throughout the study. MAS children will be recruited at the UNTA level, whether they come directly from the community or whether they are referred from preschool consultations (CPS). Community intermediaries will ensure awareness-raising on acute malnutrition in order to facilitate recruitment on time. The list of names of the children participating in the study with their identifier will be kept under lock and key in each health center, in order to guarantee confidentiality throughout the study. MAS children will be recruited at the UNTA level, whether they come directly from the community or whether they are referred from preschool consultations (CPS). Community intermediaries will ensure awareness-raising on acute malnutrition in order to facilitate recruitment on time.

A total of 1000 SAM children aged 6-59 months will be recruited from 14 UNTAs for this study. Randomization will be individual and will be done at the level of each UNTA.

## Abbreviations

|          |                                                                                                                                                                                    |
|----------|------------------------------------------------------------------------------------------------------------------------------------------------------------------------------------|
| ACF      | Action against Hunger                                                                                                                                                              |
| IYCF     | Nutrition for Young Children                                                                                                                                                       |
| RUTF     | Ready-to-use therapeutic food                                                                                                                                                      |
| CS       | Health center                                                                                                                                                                      |
| CPS      | Preschool consultation                                                                                                                                                             |
| DPM      | Psychomotor Development                                                                                                                                                            |
| DSMB     | Data and Safety Monitoring Board - patient safety committee (1 nutrition specialist + 1 biostatistician)                                                                           |
| ESP      | School of Public Health                                                                                                                                                            |
| AND      | Standard deviation (SD)                                                                                                                                                            |
| IT       | Registered Nurse                                                                                                                                                                   |
| ID       | Username                                                                                                                                                                           |
| MANGO    | Modeling an Alternative Nutrition protocol Generalizable to Outpatient , Name of the Burkina research project that demonstrated the effectiveness of a reduced dose of RUTF |
| MAS      | Severe Acute Malnutrition                                                                                                                                                          |
| MCZS     | Head of Health Zone                                                                                                                                                                |
| WHO      | World Health Organization                                                                                                                                                          |
| NGO      | Non Governmental Organization                                                                                                                                                      |
| PT       | Weight - Size index                                                                                                                                                                |
| PB       | Brachial Perimeter                                                                                                                                                                 |
| PCIMA    | Integrated Management of Acute Malnutrition                                                                                                                                        |
| PRONANUT | National Nutrition Program                                                                                                                                                         |
| DRC      | Democratic Republic of Congo                                                                                                                                                       |
| RDPM     | Psychomotor Developmental Delay                                                                                                                                                    |
| RECO     | Community Relays                                                                                                                                                                   |
| Unicef   | UNICEF                                                                                                                                                                             |
| UNTA     | Outpatient Therapeutic Nutritional Unit                                                                                                                                            |
| UNTI     | Intensive Therapeutic Nutritional Unit                                                                                                                                             |
| ZS       | Health Zone                                                                                                                                                                        |

# **I. Introduction**

## **1.1. Context and rationale**

More than 47 million children suffered from acute malnutrition around the world before the COVID 19 pandemic (1) mostly in low- and middle-income countries, particularly in Africa and Asia(2). According to estimates, around 10.4 million new children will suffer from acute malnutrition in 2021 mainly in the Middle East (Yemen) and Sub-Saharan Africa including the Democratic Republic of Congo (DRC)(3) (4). The DRC will bear the heaviest burden because the country will account for more than 30% of this total, i.e. around 3.3 million children are said to be suffering from acute malnutrition as of now.(4). This increase would be due to the negative effects of confinement, even of short duration: disruption of economic systems with a reduction in GDP per capita of 6 to 7% (standard deviation 2-4%), decrease in access to health services and nutrition in low and middle income countries(3) (5).

The increase in the number of children suffering from acute malnutrition would be accompanied by an approximately 25% reduction in access to health and nutrition services, experts estimate there will be more than 128,605 additional deaths in children under 5, more than 52% of which came from Sub-Saharan Africa (6).

The consequences of the pandemic would also lead to an increase in the number of people living under the extreme poverty line, approximately 140 million additional individuals. (5) and lead to a situation of acute food insecurity reaching 265 million people (7). Access to basic social services, including health and nutrition, has also experienced a sharp decline following the COVID 19 pandemic, like what happened with the great Ebola epidemic in Africa. the west(8).

It is in this context that the leaders of four United Nations agencies (UNICEF, FAO, WFP and WHO) launched an urgent appeal "Child malnutrition and COVID-19: the time to act is now"(9)in which they propose 5 urgent actions to be implemented to limit the impact of COVID-19 on infant nutrition: i) Safeguard and promote access to nutritious, safe and affordable food; ii) Invest in improving maternal and child nutrition during pregnancy, childhood and early childhood; (ii) Reactivate and strengthen services for the early detection and treatment of wasting and the treatment of wasting in children; iv) Maintain the provision of nutritious and safe school meals for vulnerable children; and v) Develop social protection to ensure access to nutritious food and essential services(9).

The 3rd recommendation of the heads of the United Nations agencies concerns the early detection and treatment of wasting (acute malnutrition) in children(9). This work is only interested in severe acute malnutrition (SAM) which is defined by a very low weight-for-height index (PT) lower than  $-3$  z-scores at the median, indicative of severe and visible wasting, and / or by a low MUAC of less than 115 mm and / or by the presence of bilateral nutritional edema on the feet(10). Acute malnutrition occurs when the body is deprived of calorie and micronutrient intake due to insufficient food intake, poor nutrient absorption due to illness or anorexia, for a relatively short time. Children under five are most vulnerable to malnutrition(11) because of their nutritional needs increased by growth and immunity not yet acquired in the face of various common pathologies (respiratory, digestive).

The management of acute malnutrition has two components: systematic medical treatment and nutritional treatment. In addition to routine antibiotic therapy and deworming, medical treatment includes vaccination against measles and vitamin A supplementation.(12). In addition, any childhood illness identified on admission such as malaria, scabies, diarrhea, etc. receives appropriate treatment during the treatment of SAM.

The nutritional treatment of severe acute malnutrition consists essentially of the administration of ready-to-use therapeutic foods (RUTF). For children who suffer from SAM without complications, the management is done on an outpatient basis with RUTF, a peanut paste enriched with powdered milk, vegetable oils, sugars, vitamins and minerals.(13) (14), according to the strategy of integrated management of acute malnutrition (PCIMA) unlike previous protocols where children were treated with F75 and F100 milks in a hospital environment (15) (16) (14).

A series of bottleneck analyzes (17)carried out in the West and Central Africa region in 2018 documented key issues regarding the delivery and uptake of outpatient SAM care. Major issues include lack of trained human resources, support costs, long waiting times, stockouts and geographic access. RUTF stock-outs are one of the obstacles to accessing and participating in the PCIMA program. These ruptures would be due to the large volume and the difficulties encountered in the transport of RUTF(18). In the DRC, for example, only 15 to 20% of children suffering from acute malnutrition, i.e. 495,000 to 660,000, could have access to acute malnutrition treatment services.(19). Because all of the countries (73 in total) that benefit from the PCIMA program are totally dependent on UNICEF or the Clinton Foundation, it is difficult

to ensure the sustainability of the PCIMA. The high cost of RUTF (around 50% of the total cost of PCIMA), would prevent respective governments from ensuring their own supply(20).

It is in this context that the actors in the field have implemented adaptations of the protocol to face the constraints encountered. In Niger, MSF distributed 2 sachets of RUTF (1000 kcal) to more than 328 children aged 6 to 59 months, of whom more than 90% were aged 12 to 35 months. The beneficiaries showed a weight gain of  $9.8 (\pm 4.6)$  g / kg / day for an average duration of treatment of  $29 (\pm 13.5)$  days(21). This was also the case during an intervention in Burma in 2009, the NGO Action Contre la Faim (ACF) provided treatment for severe acute malnutrition without medical complications with reduced doses of RUTF. Until children reached a PT index  $\geq -3$  and MUAC  $\geq 110$  mm, the dosage was based on the child's weight. Afterwards, 500 kcal / day or 1 sachet of RUTF per day (until discharge) was distributed to each child regardless of their weight. A weight gain velocity of 4 g / kg / day (3 to 5.7 kg) was observed for each child for an average duration of treatment of 42 days (28 to 56 days). This experience in Burma shows that it is possible,(22). It should be noted that in practice it is observed the sale or sharing of RUTF distributed to children within the framework of the PCIMA.(23). This implies that children sometimes actually consume less RUTF than what is distributed.

The evaluation carried out on 3083 children in Myanmar between 2009 and 2010 showed that a reduced dose of RUTF, associated with routine care, allows to have the same effectiveness as the standard dose. In the outlook, this study recommended carrying out similar but randomized research to verify the effectiveness of a reduced dose of RUTF for the management of SAM.(22).

The recent results of the MANGO study, carried out in Burkina-Faso, showed that the reduction in the dose of RUTF after two weeks of treatment of children suffering from SAM, defined by PT  $< -3$ zscore and / or MUAC  $< 115$  mm and no edema at all, reduced neither weight gain (3.4 g / kg / day; 95% CI -0.4 to 0.4;  $p = 0.92$ ) nor rate of girth gain brachialis (BP), does not affect healing or prolong the duration of treatment (with a median of 56 days; interquartile range [IQR] 35-91) although a small negative effect (0.2 mm / week; 95% CI: 0.04 to 0.4;  $p = 0.015$ ) was observed on linear growth especially for the youngest subjects (24). This study was able to show that children with a reduced dose of RUTF had the same body composition as those who received the standard dose, and came out cured with a fat-free mass almost at the same level as that of healthy children in the community.(25). In terms of energy, reducing the dose

of RUTF leads to a reduction in the daily intake but nevertheless makes it possible to cover the daily energy needs of children treated for uncomplicated SAM.(26).

The MANGO study demonstrates that a reduced dose of RUTF would be as effective as the standard dose in the management of uncomplicated SAM under ideal conditions. It is in this context that we propose to carry out the EfRAMAS project to confirm this in a situation of food insecurity and without additional staff to collect data on children who suffer from SAM in the DRC.

## **1.2. Purpose and Objectives**

### **Goal**

The aim of this study is to help improve the management of severe uncomplicated acute malnutrition.

### **Goals**

#### **a. Main objective**

To assess the effectiveness of a reduced dose of RUTF in children 6 to 59 months with SAM (defined by PT  $<-3$ zscore and / or MUAC  $<115$ mm and / or edema +, ++) without complications in a context of 'food insecure and no additional staff to collect data.

#### **b. Specific objectives**

##### **Primary objective**

To assess the effectiveness of a reduced dose of RUTF in the management of SAM in children aged 6 to 59 months on the rate of weight gain (g / kg / d) from admission to discharge .

##### **Secondary objectives**

To assess the effectiveness of a reduced dose of RUTF in the management of SAM in terms of:

- **Duration of edema melting** (in days) since admission.
- **Duration of stay** (in days);
- **Performance indicators (cure rate, dropout, mortality, non-respondent, transfer to hospital)**
- **Treatment cost savings** (average cost and total cost per child treated);
- The growth velocity of anthropometric indices
- **Psychomotor development** children
- **Degree of acceptance** a reduced dose of RUTF by healthcare workers and the community
- **Relapse rate** up to 3 months after the “cured” exit from the program.

## **Research hypotheses**

### **Main hypothesis**

Children receiving the reduced dose will have the same weight gain from admission to discharge as children receiving the standard dose of RUTF with a non-inferiority margin of 0.5g / kg / day.

### **Secondary assumptions**

- Children receiving the reduced dose of RUTF will have the same performance indicators (cure rate, death, drop-out, relapse) as those receiving the standard dose;
- Children receiving the reduced dose of RUTF will have the same length of stay as those receiving the standard dose;
- Children receiving the reduced dose of RUTF will have the same psychomotor development as those receiving the standard dose;
- Treatment with a reduced dosage of RUTF will be less expensive than treatment with the standard dose.

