### 2.1.6. Sample size

The size needed for this work will be calculated according to the following formula:

$$N = (Z_{1-\alpha} + Z_{1-\beta})^2 \times 2 \sigma^2 / (\Delta - \delta)^2$$

Or :

$\alpha$  represents the error of the first kind;  $\beta$ , error of the second kind;  $\Delta$ , the Non-inferiority Margin;  $\sigma^2$ , Estimation of the variance and  $\delta$ , Possible difference in expected efficacy between the standard dose and the reduced dose. As  $\alpha = 0.05$  then  $Z_{1-\alpha} = 1.64$  and  $Z_{1-\beta} = 0.84$  (38) (39) (40).

In this study the mean rate (SD) of weight gain for each participant is 5 g / kg / day (2.6) and the expected difference between the two groups (control and intervention groups) will be 0 g / kg / day with a non-inferiority of 0.5 g / kg / day. The minimum acceptable average rate of weight gain in any group will be 4.5 g / kg / day. Assuming a power of 80% and a significance level of 5%, 335 children are needed in each group to verify that the maximum true difference between the intervention groups is not more than 0.5 g / kg / day . Taking into account a dropout rate of 20%, the total sample size was rounded to 1,000 children.

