### **2.3.3. Statistical analyzes**

For the quantitative part of the study, the data will be summarized in Mean and Standard Deviation if they are normally distributed (normality test) for continuous variables and in absolute and relative frequencies for categorical variables.

The t-test and the chi-square test will be used respectively to compare the means and the proportions of the socio-demographic characteristics at admission for the quantitative and qualitative variables.

Linear regression analyzes will be used to determine the significant differences between the 2 groups of children for the quantitative variables.

Binary logistic regression analyzes will be used to determine the significant differences between the 2 groups of children for the binomial qualitative variables (2 response modalities).

Multinomial logistic regression analyzes will be used to determine the significant differences between the 2 groups of children for the multinomial qualitative variables (3 or more modalities).

All analyzes will be done in an adjusted and unadjusted model and a difference is statistically significant when the P-value is less than 0.05.

The results will be analyzed using statistical software, in this case STATA, version 17.

The main analyzes will be done by intention to treat (ITT) and per protocol for the main result, in this case, the speed of weight gain. The other secondary results will be analyzed only by intention to treat (ITT).

For the DPM, a score will be assigned to the participant and the sum will constitute the total score for each participant per domain.

For focus group data, after transcription of the recordings into Word 2019, thematic analysis will be done using Excel tables (matrix) or Nvivo® software.

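### The protocol hypothesises the same cure, death, drop-out and relapse on the reduced dose without a margin, and provides only a P<0.05 test of difference, which cannot show sameness

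*Protocol*

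**What the plan says.** Under Research hypotheses, the Main hypothesis predicts equal weight gain in the two groups "with a non-inferiority margin of 0.5g / kg / day". The Secondary assumptions that follow use the same language of sameness for the programme outcomes. Children on the reduced dose "will have the same performance indicators (cure rate, death, drop-out, relapse) as those receiving the standard dose". No margin is attached.

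Section 2.3.3 fixes the method for two-category outcomes: "Binary logistic regression analyzes will be used to determine the significant differences between the 2 groups of children". Outcomes with three or more categories get multinomial logistic regression for the same purpose. The rule for every comparison is that "a difference is statistically significant when the P-value is less than 0.05".

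Section 2.1.6 sizes the main trial on weight gain only: "Assuming a power of 80% and a significance level of 5%, 335 children are needed in each group", rounded to 1,000 in total after a 20% drop-out allowance. Annex 5 (Study population) confirms 500 per arm.

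Annex 5 also selects the type of economic analysis: cost minimisation if the non-inferiority hypothesis is verified, otherwise cost-effectiveness. Its section on efficacy data names the cure rate as the main outcome of interest.

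**The concern.** A test of difference can reject sameness but cannot establish it. For weight gain the protocol deals with this by setting a margin. For cure, death, drop-out and relapse it keeps the sameness hypothesis and drops the margin. The protocol offers no other criterion for judging that hypothesis, so the only outcome that could appear to support it is P≥0.05. That result may mean no harm, or too few children to see the harm.

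There is a consequence inside the protocol. Cost minimisation treats the two strategies as equally effective. Annex 5 triggers it by non-inferiority, and the only non-inferiority hypothesis with a margin concerns weight gain. Cure, which Annex 5 makes its main outcome, could therefore be treated as equal without ever having been tested for non-inferiority.

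**Working it through.** **1. The protocol's own figure.** With margin 0.5, SD 2.6, true difference 0, one-sided 5% and 80% power:

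n = 2 × 2.6² × (1.645 + 0.842)² / 0.5² = 335 per group.

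This agrees with section 2.1.6 (the rounded values 1.64 and 0.84 give 333). With 20% drop-out, 335 / 0.80 = 419 per arm, or 838 in total, so 1,000 is a generous rounding. None of these inputs concerns a binary outcome.

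**2. Inputs for the binary outcomes.**
- 500 per arm: Annex 5.
- Cure: the only figure is background text in Annex 4, which says that outpatient cure is often above 75%. That is a floor and not a planning value, so 75%, 85% and 90% are tried.
- Drop-out: 20% in section 2.1.6 is a sample-size allowance and not a predicted outcome rate, so 10% and 20% are tried.
- Death (1 to 2%) and relapse (5 to 10%): assumptions, because the protocol gives no control rate.
- Relapse is counted among cured children: 0.75 × 500 = 375 per arm.

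**3. Chance of missing a difference.** For a two-sided 5% test of two proportions with n per arm, difference d and mean rate p̄:

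power = Φ[(d − 1.96 × SE₀) / SE₁], where SE₀ = √(2p̄(1−p̄)/n) and SE₁ = √([p₁(1−p₁) + p₂(1−p₂)]/n).

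Example, cure 75% v 70%: SE₀ = √(2 × 0.725 × 0.275 / 500) = 0.02824 and SE₁ = 0.02820. Then (0.05 − 0.05535) / 0.02820 = −0.19, power is 42.5%, and 57.5% is missed.

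| Outcome | Standard v reduced | n per arm | Power | Missed |
|---|---|---|---|---|
| Cure | 75% v 70% | 500 | 42.5% | 57.5% |
| Cure | 85% v 80% | 500 | 55% | 45% |
| Cure | 90% v 85% | 500 | 67% | 33% |
| Cure | 75% v 67% | 500 | 80% | 20% |
| Cure | 75% v 65% | 500 | 93% | 7% |
| Death | 1% v 2% | 500 | 25% | 75% |
| Death | 2% v 4% | 500 | 46% | 54% |
| Drop-out | 10% v 15% | 500 | 67% | 33% |
| Drop-out | 20% v 25% | 500 | 47% | 53% |
| Drop-out | 20% v 30% | 500 | 96% | 4% |
| Relapse | 5% v 10% | 375 | 74% | 26% |
| Relapse | 10% v 15% | 375 | 54% | 46% |
| Relapse | 10% v 20% | 375 | 97% | 3% |

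Simulating the test for the two death rows gave power of 24% and 46%, close to the formula. If only 400 per arm were analysable, the misses would rise to about 65% for cure 75% v 70%, 30% for cure 75% v 67%, 79% for death 1% v 2% and 62% for death 2% v 4%.

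**4. What an interval would show.** If both arms had the same observed rate p, the 95% half-width is 1.96 × √(2p(1−p)/n). That is 5.4 points for cure at 75% (n = 500), 1.7 points for death at 2% (n = 500) and 4.3 points for relapse at 10% (n = 375). Even identical observed rates would leave excesses of that size not excluded.

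**The case against.** The strongest reply is that the protocol nowhere says a non-significant result will be reported as sameness. The Main hypothesis also uses the word loosely and still carries a margin. Logistic regression yields confidence intervals, and their reporting for secondary outcomes is often left to a statistical analysis plan, which is not shown. Section 2.4.1 provides a monthly safety review that can recommend changing or stopping the study. Section 3.9 says the results are guidance and do not themselves change the national protocol.

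Much of this is fair. It is an inference that P≥0.05 would be written up as sameness; the protocol does not state it. Its force is only that no other criterion is given. The safety review and the limited policy claim reduce the consequences, but neither supplies a criterion for the hypothesis. A later plan could add intervals, but it would still inherit a sameness hypothesis paired with a test that can only reject it.

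A reader might also infer that a clinically important harm would usually go unnoticed. The documents do not support that. They define no clinically important difference for these outcomes and no control rate for death or relapse, and the table shows that larger harms would mostly be found. For a 5-point cure loss, the answer turns on the control rate: missed more often than not from 75%, but not from 85% or 90%.

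**Conclusion.** The point holds as a mismatch between hypothesis and test. Cure, death, drop-out and relapse are hypothesised to be the same with no margin, and the only stated rule is a P<0.05 test of difference, so a non-significant result cannot support the hypothesis.

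The size depends on the outcome. Weak detection is clearest for death: a doubling from 1 to 2% would be missed 54 to 75% of the time at 500 per arm. A 5-point cure loss would be missed between 33% and 57.5% of the time across control rates of 90% down to 75%. A cure loss of about 8 points or more from 75% would be missed 20% of the time or less, and 10-point rises in drop-out or relapse 3 to 4%. The death and relapse rates are assumptions, and the cure and drop-out rates are borrowed from text that does not offer them as predictions. The primary weight-gain comparison is not affected.

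**What to change.** In Secondary assumptions, replace the claim of the same performance indicators with an aim to estimate the between-group differences in cure, death, drop-out and relapse.

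In section 2.3.3, state that for these four outcomes the report will give the risk difference with its 95% confidence interval and the largest harm not excluded, and that P≥0.05 will not be read as sameness.

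If the investigators want to claim non-inferiority on cure, including to justify cost minimisation in Annex 5, they should fix a margin before unblinding, justify it clinically, and judge it by the confidence limit. No margin is proposed here; its size is theirs to defend.

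The cost is wording in two sections and intervals in the tables, with no extra children or data. The downside is that the report can no longer claim the same mortality, drop-out or relapse.
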